### Recruitment {15}

Participants will be identified and recruited through the P3 Cohort, which will engage participants through ultrasound clinics, outpatient obstetric clinics, obstetrical triage, and advertising in the community. An informational postcard will be shared by clinic staff with potential participants, who will then be able to self-refer by providing their contact information to be contacted by a member of the P3 study team. Online advertising will contain a link to register for more information about the study, and participants will subsequently be contacted by the study team.

## Assignment of interventions: allocation

### Sequence generation {16a}

Participants will be randomized using computer-generated blocked randomization (block size 4) in a 1:1 ratio to the intervention group or the control group. 123 participants will be randomized into each study group, with a total of 246 participants enrolled in the RCT.

### Concealment mechanism {16b}

The randomization list and participant group assignments will be saved in a password-protected file saved on a secure server. Only research assistants on the P3 study team who are not involved in the analysis for the trial, and therefore unblinded, will have access to the file. Participant blinding is not possible with informed consent for a behavioural intervention.

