### Who will take informed consent? {26a}

All prospective participants will complete informed consent electronically to participate in the primary P3 cohort, which will include optional consent to be contacted and screened for inclusion in sub-studies, including this nested trial. Those meeting the AD definition (above) will be invited to complete a brief screening questionnaire for the current trial. Once it is determined that a prospective participant is eligible to participate, they will be contacted by trained research assistants, who will explain the study procedures in full detail, provide the participant with written copies of the consent form, and obtain written informed consent for participation in the nested trial.

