#### Screening and enrollment

After informed consent is obtained for the P3 cohort, including consent to be contacted for nested trials, participants meeting the study definition of AD will be identified by research assistants using weekly data queries. For the purposes of this study, AD is defined as a score of 10 or greater on the Edinburgh Postnatal Depression Scale (EPDS), which has been validated to measure major depressive disorder against diagnostic interviews (sensitivity 87.7%; specificity 90.9%) in pregnant individuals [34, 35]. All participants with AD will be invited to join this nested trial. Participants will be contacted by trained research assistants, provided with study information, and invited to enrol in the current study.

Written informed consent will be obtained in addition to the P3 cohort consent. Research assistants will screen participants further for eligibility and included participants will be randomized to receive the intervention or standard of care (control). Randomization will be conducted using computer-generated, block-randomization into an intervention group and a control group (receiving standard of care).

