### Implementation {16c}

A senior research coordinator with experience in randomized trials will be unblinded to study allocations. The coordinator will conduct randomization and generate an allocation list, with the support of a biostatistician external to our study team. P3 research assistants will then notify peer counsellors of their assigned participants as they enrol and provide necessary contact information.

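### The concealment rule bars list-holders from the analysis but not from recruitment, and fixed blocks of four make part of the sequence predictable

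*Protocol article*

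**What the plan says.** All references are to the protocol article.

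- **List and access, {16b}.** "The randomization list and participant group assignments will be saved in a password-protected file saved on a secure server". Access is then given to a defined group: "Only research assistants on the P3 study team who are not involved in the analysis for the trial", who are described as "and therefore unblinded, will have access to the file".
- **Sequence, {16a}.** Allocation uses "computer-generated blocked randomization (block size 4) in a 1:1 ratio", for 246 participants, 123 per arm. No stratification is mentioned.
- **Recruitment, Screening and enrollment.** "participants meeting the study definition of AD will be identified by research assistants using weekly data queries". Later in the same section: "Research assistants will screen participants further for eligibility and included participants will be randomized".
- **Consent, {26a}.** Once candidates are found eligible, "they will be contacted by trained research assistants, who will explain the study procedures in full detail", and the same staff obtain written consent.
- **Implementation, {16c}.** An unblinded senior research coordinator randomizes and generates the list, supported by a biostatistician from outside the team. After that, "P3 research assistants will then notify peer counsellors of their assigned participants as they enrol".
- **Blinding, {17a}.** Investigators are blinded. Participants, peer counsellors, clinical supervisors and one research assistant, who is responsible for randomization and coordination, are not.

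**The concern.** Allocation concealment means that whoever decides whether and when a person enters the trial cannot know the arm that comes next. Section {16b} is where the article should secure this, but the only condition it sets for opening the list is having no part in the analysis. A research assistant who recruits and never touches the analysis meets that condition.

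A recruiter who knows or can guess the next arm can hurry, delay, encourage or discourage a candidate. The arms may then differ at entry in ways nobody recorded. The planned adjustment for imbalance in {20a} reaches only measured variables. Intention-to-treat analysis in {20c} does not help either, because the selection happens before randomization. Gestational age taken from health records is measured objectively, but that protects the measurement and not the composition of the arms. The primary comparison is therefore exposed along with the self-reported outcomes.

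**Working it through.** The plan states no figure on this point, so there is none to reproduce. The check has two parts.

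**1. Roles side by side**

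| Task | Who | Section |
|---|---|---|
| Identify candidates, screen | Research assistants | Screening and enrollment |
| Explain the trial, obtain consent | Trained research assistants | {26a} |
| Open the file with list and assignments | P3 research assistants not in the analysis | {16b} |
| Randomize, generate the list | Senior research coordinator, with external biostatistician | {16c} |
| Tell counsellors their assignments | P3 research assistants | {16c} |
| Unblinded study staff (besides counsellors and supervisors) | One research assistant responsible for randomization and coordination | {17a} |

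No section states that the people in the first two rows are kept apart from those in the third. The unblinded role is several research assistants in {16b}, a coordinator in {16c}, and a single research assistant in {17a}.

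**2. Predictability**

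*With the file:* every upcoming allocation can be read, so 100%. This applies only if a recruiter has access.

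*Without the file, seeing all past assignments in order, block fixed at 4, ratio 1:1.* There are 6 equally likely balanced sequences per block. The best strategy is to guess the arm that is behind.

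| Position in block | Certain | Best guess correct |
|---|---|---|
| 1 | 0 | 1/2 |
| 2 | 0 | 2/3 |
| 3 | 1/3 (first two match) | 1/3 + (2/3 × 1/2) = 2/3 |
| 4 | 1 | 1 |

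- Known with certainty: (1/3 + 1)/4 = 33.3%. Over 246 allocations, 246 × 1/3 = 82.
- Guessed correctly: (1/2 + 2/3 + 2/3 + 1)/4 = 70.8%. Over 246, 246 × 0.708 ≈ 174.
- Under full concealment a guess is right 50% of the time, or 123 of 246.

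*Effect of varying the blocks.* Block sizes of 4, 6 and 8 chosen at random are an assumption, since the article gives no such set. In 4,000 simulated lists of 246, with a guesser who always names the arm that is behind, 68.0% of guesses were correct. The same simulation with fixed blocks of 4 gave 70.7%. Varying the blocks therefore gains just under 3 percentage points.

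**The case against.** The strongest reply is that overlap of roles is inferred. The recruiting sections speak of research assistants in general, while {16b} speaks of a limited set on the P3 team. Section {16c} gives randomization to a coordinator with outside support, and {17a} names a single unblinded assistant. A small, dedicated unblinded role is a fair reading, and a journal article may leave delegation of tasks to the full protocol.

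Part of this stands. A reader might infer that the list is open to the very people who consent participants, or that all allocations are foreseeable by design. The article supports neither. It shows a shared job title and no stated separation, and 100% is only the worst case. A reader might also call the trial unblinded; the article calls it single-blinded, with investigators blinded.

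What does not stand is the idea that nothing is wrong until delegation is known. The article does not merely omit a rule. It states one, under the concealment heading, and the criterion chosen serves a different purpose.

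Two further points narrow the concern without removing it:

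- **Order of events.** The EPDS score comes from the cohort questionnaire that identifies candidates, and consent and screening precede randomization (Week 1, then Week 2 in {13}). So it cannot be said that assignments are made before enrolment. But this order does not hide a list that someone can already read.
- **Limited discretion.** Candidates come from data queries, and everyone who meets the depression definition is to be invited. Persuasion, timing and eligibility judgements can still vary.

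The 33% and 71% figures also need a recruiter who sees the whole sequence in order. The article says P3 research assistants relay assignments to counsellors; it does not say that recruiters track them.

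**Conclusion.** The point holds as a fault in the stated access rule. Section {16b} restricts the list by role in the analysis, no section separates list-holders from recruiters, and three sections disagree on who is unblinded. The coordinator and external biostatistician protect how the list is made, and the password protects how it is stored. Neither conceals it from a research assistant who has been given access.

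The size depends on who does what in practice:

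- If no recruiter has access to the file or sees past assignments, there is no bias and the text needs only correction.
- If a recruiter sees all past assignments in order, 33% of allocations are certain and 71% are guessable, against 50%.
- If a recruiter can open the file, up to 100% can be known.

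These figures measure opportunity for selection, not bias in days of gestation, which the documents give no means to estimate. The change is worth making because it is cheap and the analysis cannot repair this kind of bias afterwards. Confidence is moderate, since actual delegation is not shown.

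**What to change.** 1. Rewrite the access rule in {16b} so that nobody who invites, screens or consents candidates can open the randomization list. Exclusion from the analysis can stay as an additional condition.
2. Have the senior coordinator or the external biostatistician hold the list and release one assignment at a time, only after that person's consent and eligibility have been recorded.
3. Make {16b}, {16c} and {17a} agree on which roles are unblinded and how many people fill them.
4. As a minor addition, use randomly varying block sizes and do not disclose them to recruiting staff. Alone this does little (about 71% to 68% guessable with the assumed 4/6/8 mix), so it cannot replace steps 1 and 2.

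**Cost.** If the roles are already separate, steps 1 to 3 amount to a few sentences. If not, they require moving file access and setting up a release procedure. Step 4 allows slightly larger imbalance at the end. Since 246 is 61 blocks of 4 plus 2, fixed blocks stopped at 246 can already end at 124 to 122. A block of 8 stopped after four identical assignments would give 125 to 121. Neither has practical weight.

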### Implementation {16c}

A senior research coordinator with experience in randomized trials will be unblinded to study allocations. The coordinator will conduct randomization and generate an allocation list, with the support of a biostatistician external to our study team. P3 research assistants will then notify peer counsellors of their assigned participants as they enrol and provide necessary contact information.

## Assignment of interventions: blinding

### Who will be blinded {17a}

The study investigators will be blinded. The participants, peer counsellors, and clinical supervisors will not be blinded to the study. Lastly, the research assistant responsible for randomization and study coordination will not be blinded.

### Procedure for unblinding if needed {17b}

Not applicable, as participants, peer counsellors, and clinical supervisors will not be blinded.

## Data collection and management

### Plans for assessment and collection of outcomes {18a}

#### Primary outcome

*Gestational age at delivery* will be collected from linked hospital records. Participants will be asked upon enrollment to the P3 cohort to consent to data linkage and hospital chart review to provincial health care databases for themselves and their infant. Standardized medical information, including gestational age at delivery, NICU admission, length of stay, and hospital readmission, will be collected.

#### Secondary outcomes

*Symptoms of depression* will be measured using the Edinburgh Postnatal Depression Scale (EPDS). The EPDS is a 10-item questionnaire that will be administered at less than 27 weeks gestation (T1), 34–36 weeks’ gestation (T2, post-intervention), 5–6 months postpartum (T3), and 11–12 months postpartum (T4). The EPDS has been validated to measure major depressive disorder against diagnostic interviews in pregnant individuals and is a valid and reliable measure of symptoms of depression during the perinatal period [34, 35, 43].

#### Symptoms of anxiety

*Symptoms of anxiety* will be measured using the PROMIS anxiety 7a-item short form [41]. The PROMIS anxiety 7a-item short form is a questionnaire that provides a valid and reliable measure of symptoms of anxiety, including when administered with a perinatal population [34, 41]. The PROMIS anxiety 7a-item short form will be administered at T1, T2, T3, and T4.

#### Lived experiences of delivering the peer-intervention

*Lived experiences of delivering the peer-intervention* will be measured using thematic analysis of qualitative transcript data. Individual in-depth interviews will elicit reflective conversation around the experiences of peers in delivering the intervention, and any perceived positive or negative impacts the experience may have on their well-being. We will also explore their thoughts and opinions on strengths and weaknesses of the intervention and its delivery (including the training experience) and whether they have suggestions for improvement in the future (Additional file 2: Appendix B qualitative interview guide)

#### Descriptive measures

*Demographic data* will be collected at baseline (T1) and will include age, work status, education, experiences of everyday discrimination and Hunger Vital Signs*.* Data on medication use will also be collected at study enrollment, as part of the eligibility criteria.

### Plans to promote participant retention and complete follow-up {18b}

Peer counsellors will contact participants to book weekly remote-counselling sessions. Feedback gathered from the P3 Cohort parent advisory council will inform participant retention strategies, including reminders for questionnaires, congratulatory e-cards following the birth of their infant, and regular communication. In our patient-oriented pilot study including over 140 participants, over 80% of the sample was retained over 1 year [29].

### Data management {19}

In accordance with the University of Calgary’s Data Retention Policy, data will be stored on a secure server in compliance with TCPS-II guidelines, to which only the primary investigators and study team will have access.

### Confidentiality {27}

The confidentiality of participant data and identity will be protected in accordance with the University of Calgary ethics guidelines throughout the recruitment, assessment, treatment, and data analysis. All members of the study team, including peer counsellors, will sign a confidentiality and non-disclosure agreement prior to their involvement in the study. Peer counsellors will be required to sign non-disclosure agreements, and instructed to store participant identifying information on a secure password-protected device to which they have sole access. All participant identifying information will be password-protected and stored on secure servers at the University of Calgary, separate from anonymized data.

Participants will be informed of the limits to confidentiality as part of the informed consent process. Participants will also be informed that absolute confidentiality cannot be guaranteed in a remote environment, as information transmitted via the internet or using personal devices (e.g. the participant’s cell phone) may not be completely secure.

### Plans for collection, laboratory evaluation and storage of biological specimens for genetic or molecular analysis in this trial/future use {33}

Not applicable, as no biological specimens will be collected.

## Statistical methods

### Statistical methods for primary and secondary outcomes {20a}

We anticipate that the block randomization will successfully eliminate confounding by covariates, but potential confounding variables will be measured on all questionnaires, and imbalance between intervention and control groups assessed prior to the final analysis. Any imbalance in confounding variables between the groups will be controlled for as appropriate, using cox proportional hazards or logistic regression modelling. Descriptive statistics will be calculated for all participant characteristics that have the potential to act as confounding variables on the primary association between the intervention and gestational age.

Time-to-event analysis will be used to assess change in our primary outcome of gestational age at delivery.

Logistic regression will be used to model the association between the intervention and categorical secondary outcome of depression (scoring 13 or greater on the EPDS), post-intervention, and 6 and 12 months postpartum. Secondary outcomes of difference in continuous scores on the EPDS (depression), PROMIS (anxiety), and parenting self-efficacy scales between intervention and control groups will be modelled using linear regression.

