### Trial design {8}

A trial within cohort design will be conducted [33]. A two-arm, single-blinded, parallel groups superiority design RCT with repeated measures will be used to evaluate the impact of remote (phone and/or online), peer paraprofessional-delivered BA and peer support on gestational length, compared to standard-of-care (SOC), among individuals with antenatal depression. Assessments will be conducted prior to 27 weeks’ gestation at trial intake (T1), within 1 week of inervention completion and prior to delivery (T2), 5–6 months postpartum (T3), and 11–12 months postpartum (T4). The current study will be conducted in adherence with the University of Calgary’s Conjoint Health Research Ethics Board (CHREB) regulations, and the 1964 Helsinki Declaration, and reported in accordance with CONSORT guidelines.

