## Interventions

### Explanation for the choice of comparators {6b}

An SOC control group will be used as a comparator, as it would be unethical to deny care to any person that is identified as being depressed, once screened for inclusion in our study. The standard of care for depression in Alberta includes provision of resources to seek mental health care, in the form of telephone numbers and the Alberta Health Services Website. Any care is then self-initiated by the participant. This comparison will allow for the best estimate of the potential population impact of our study intervention in Alberta.

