### Relevant concomitant care permitted or prohibited during the trial {11d}

Information on concomitant care will be gathered and tracked throughout the study to ensure that participants receiving care are evenly disbursed between groups. Inclusion will be restricted to individuals who meet the eligibility criteria and who do not have any current active treatment regimen for a diagnosed mental illness (e.g. medications and/or counselling), with the exception of participants who have been on a stable dose of anti-depressant medications (e.g. SSRIs) for 3 months or more. Participants receiving other psychological interventions for mental health problems, including depression and anxiety, will be excluded from the study.

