### Participant timeline {13}

The overall participant timeline is illustrated in Fig. 1.

Week 1 (T1): Participants of the P3 Cohort study will complete a baseline assessment during pregnancy (less than 27 weeks GA). Individuals who are eligible for this study will be identified and will be contacted by a member of the study team to be invited to participate. The study team member will outline the study protocols and obtain informed consent.

Week 2: Participants will be randomly assigned, using computer-generated block randomization, into the intervention group or the standard of care control group.

Weeks 3–6: Participants randomized to the intervention group will complete the BA counselling sessions with a peer counsellor via telephone, in addition to regular informal peer-support contact. Participants in the control group will continue to receive standard of care.

Week 8–10 (T2): At 34 to 36 weeks gestation, after the completion of the intervention, all participants will be invited to complete an electronic P3 Cohort questionnaire.

Post-due-date (up to 6 weeks postpartum): After childbirth, information about gestational age at delivery will be collected for the P3 cohort via linkage to the participant medical record. Participants will continue to have informal peer-support (social support, advice, information sharing) contact with peer counsellors via text and telephone, up to 6 weeks postpartum.

Five to 6 months postpartum (T3): All participants will be invited to complete an electronic questionnaire as part of their participation in the P3 Cohort.

Eleven to 12 months postpartum (T4): All participants will be invited to complete an electronic questionnaire as part of their participation in the P3 Cohort.

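### Covariates are chosen by observed imbalance and are not limited to values measured before randomisation; a fixed baseline set should replace this rule

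*Protocol article*

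**What the plan says.** Section {20a} of the protocol article (Statistical methods for primary and secondary outcomes) expects block randomisation to remove confounding. It then adds a safeguard: "potential confounding variables will be measured on all questionnaires, and imbalance between intervention and control groups assessed prior to the final analysis". The action that follows is: "Any imbalance in confounding variables between the groups will be controlled for as appropriate, using cox proportional hazards or logistic regression modelling". The section gives no covariate list, no criterion for imbalance, and no restriction to values taken before randomisation.

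Three other sections bear on this:

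- **Participant timeline {13}.** T1 falls in week 1. Then: "Week 2: Participants will be randomly assigned, using computer-generated block randomization". The T2 questionnaire comes later: "At 34 to 36 weeks gestation, after the completion of the intervention, all participants will be invited to complete an electronic P3 Cohort questionnaire". T3 and T4 follow at about 6 and 12 months postpartum. Three of the four questionnaires are therefore post-randomisation, and two follow delivery, which is the primary outcome.
- **Concomitant care {11d}.** "Information on concomitant care will be gathered and tracked throughout the study to ensure that participants receiving care are evenly disbursed between groups".
- **Choice of comparators {6b}.** Of standard care the protocol says: "Any care is then self-initiated by the participant".

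Under Descriptive measures, demographic data are placed at T1 and medication use at enrolment. These are not named as the adjustment set.

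**The concern.** There are two separate problems, and they have different consequences.

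**Selection by imbalance.** Under proper randomisation, a baseline difference between arms is a chance event. Its size says nothing about whether the covariate predicts outcome, which is the reason to adjust. A rule triggered by imbalance adjusts for weak predictors that happen to differ and omits strong ones that happen to be balanced. The primary model is then settled by the data rather than in advance. In Cox and logistic models, changing the covariates also changes the quantity being estimated, because hazard and odds ratios are non-collapsible.

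**No baseline restriction.** After randomisation, a difference between arms may itself be an effect of treatment. A rule that adjusts for whatever differs would tend to pick out such variables. Symptoms at T2 and care taken up during the trial are candidates: the Background gives improved psychological symptoms in pregnancy as the apparent route to less preterm birth, and care in the comparator is left to the participant. Adjusting for either could remove part of the effect that the trial is meant to estimate.

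**Working it through.** **The protocol's own figures.** None is disputed here. The sample size reproduces: 214 × 1.15 = 246.1, so 246, or 123 per group. The protocol gives no standard deviation for gestational age, so it is solved from the stated 3 days, 80% power and 5% level (taken as two-sided):

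- standardised effect d = (1.960 + 0.842) × √(2/123) = 0.357
- implied SD = 3 / 0.357 = 8.4 days

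**Illustration with baseline covariates only.** Assumed, because the protocol gives none of these: five independent baseline covariates, each correlated r with the outcome; a two-sided p<0.05 trigger for imbalance; a linear model; all 246 analysed. There were 8,000 simulated trials per setting, with d = 0.357 for power and 0 for type I error.

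The chance that at least one covariate is flagged under perfect randomisation is 1 − 0.95⁵ = 22.6%; the simulations gave 22–23%.

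| r | Type I error, imbalance rule | Type I error, fixed set | Power, imbalance rule | Power, fixed set |
|---|---|---|---|---|
| 0.2 | 4.7% | 5.5% | 80% | 87% |
| 0.3 | 3.8% | 5.2% | 82% | 96% |
| 0.4 | 2.9% | 4.9% | 83% | >99% |

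Unadjusted analysis gives 80% power throughout.

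The fixed-set power can be checked by hand. The five covariates explain R² = 5r² of the variance, and power ≈ Φ(d/√(1 − R²) × √(123/2) − 1.96):

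- r = 0.2: R² = 0.20; 0.357/0.894 × 7.842 = 3.13; Φ(1.17) = 0.88
- r = 0.3: R² = 0.45; 0.357/0.742 × 7.842 = 3.78; Φ(1.82) = 0.97
- r = 0.4: R² = 0.80; 0.357/0.447 × 7.842 = 6.26; Φ(4.30) > 0.99

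Simulation error on a 5% rate is √(0.05 × 0.95/8000) = 0.24 percentage points. The 4.7% is therefore indistinguishable from 5%, while 3.8% and 2.9% are clearly below it. The last row needs covariates that explain 80% of the variance, so it marks the far end of the range.

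**Post-randomisation values.** Here the check is one of wording. The methods section says where confounders are measured (every questionnaire) and what triggers adjustment (imbalance). It does not say which measurement is used. Three of the four questionnaires follow randomisation, so the text allows later values to enter. No sentence says that they will.

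**The case against.** **A covariate list and an imbalance criterion are commonly left to the analysis plan, and the words 'as appropriate' defer the detail.** This is fair as regards the list and the threshold. The trigger itself is not deferred: the protocol fixes imbalance as the reason to adjust, and an analysis plan that followed it would inherit the fault.

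**A baseline reading is natural.** The sentence begins with randomisation, the paragraph ends with participant characteristics, and demographics are placed at T1. This stands. A reader might infer from the reference to all questionnaires that T2–T4 values will be used, but the text says only that confounders are measured there. Nor does any passage make concomitant care a covariate; {11d} says that it is tracked, with a hope of even spread.

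**The intention-to-treat estimate is not biased by this rule.** For baseline covariates that is right: the test becomes conservative and power is lost. Bias would need adjustment for something the intervention changed, which the protocol permits but does not plan.

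**The size of any lost effect is unknown.** This also stands. For concomitant care it would depend on uptake in the control arm, where the protocol's only guide is that fewer than 20% of those with antenatal depression obtain treatment. It would also depend on how closely uptake follows distress, for which there is no guide. A percentage loss would reflect the assumptions chosen.

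**The model is not chosen on results.** Imbalance is assessed before the final analysis and investigators are blinded, so a charge of selection on outcome is not supported. The model still depends on the data through covariate balance.

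**Conclusion.** The point holds in this form: the protocol states a poor rule for choosing covariates and omits the limit to pre-randomisation values.

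With baseline covariates only, the harm is a data-driven model, lost power and a test that tends to be conservative. In the illustration, power is 80–83% under the rule against 87% to more than 99% with a fixed set. These figures rest on five independent covariates correlated 0.2–0.4 with outcome, a p<0.05 trigger and a linear model. The planned primary analysis is time-to-event, so they show the pattern and do not forecast this trial's power.

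Adjustment for variables that the intervention may have changed is a risk left open by the wording, not a stated plan, and no figure should be attached to it. The rule should be changed, since the remedy is a matter of wording.

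**What to change.** Replace the imbalance rule in {20a} with wording such as:

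> Models adjust for a fixed set of pre-randomisation variables, whatever their observed balance: baseline EPDS (and baseline PROMIS anxiety for the anxiety outcome), antidepressant use at entry, gestational age at entry, and other T1 predictors only if already collected. No variable measured after randomisation is a covariate; concomitant care is reported by arm.

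The EPDS and PROMIS anxiety scores are already taken at T1, medication use is recorded at enrolment, and gestational age must be known to judge eligibility. Parity or previous preterm birth could be added only if the cohort already records them at T1; the protocol article does not say so. Section {11d} should then give the purpose of tracking care as description by arm, since tracking cannot ensure balance.

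The cost is wording and a few degrees of freedom. In the Cox and logistic models the estimate becomes a covariate-conditional hazard or odds ratio, and the report should say so.
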